**Visit 8, week 26 (2 weeks post-4th vaccination; Window: -2 days to +14 days)**

- Clinical assessment (Adverse Event elicitation)
- Elicitation/recording of concomitant medications
- Risk behavior assessment
- Risk behavior reduction education
- Participation impact elicitation
- Post-test counseling
- Blood sample for archiving of plasma and possibly PBMCs (blood volume: 8 mL)
- Review of diary card with volunteer; enter findings on appropriate CRF

**Visit 9, week 52  $\pm$  4 weeks**

- Clinical assessment (Adverse Event elicitation)
- Elicitation/recording of concomitant medications
- Risk behavior assessment
- Participation impact elicitation
- Pre-test counseling
- Blood sample for HIV diagnosis and archiving of plasma and PBMCs (blood vol: 16 mL)

**Visits 11, 13, 15, 17, 19 corresponding to weeks 78, 104, 130, 156, 182, respectively ( $\pm$  4 wk)**

- Clinical assessment (Adverse Event elicitation)
- Elicitation/recording of concomitant medications
- Risk behavior assessment
- Participant impact elicitation
- Pre-test counseling
- Blood sample for HIV diagnosis and archiving of plasma (blood volume for each visit: 6 mL)
- For visit 19, PBMCs will also be separated and archived from this blood collection (vol: 8 mL).

**Visits 10, 12, 14, 16, 18, 20 corresponding to approximately 2-3 weeks after the 6-monthly visits**

Volunteers will go to the project clinical site approximately 2-3 weeks after Visits 9, 11, 13, 15, 17, 19 for post-test counseling, risk behavior reduction education, adverse event elicitation (including concomitant medications) and participation impact elicitation. Visit 20 will also include completion of participant impact elicitation and Termination CRF. As mentioned in section 6.3.3 the volunteer may be seen at a mutually agreed upon location for non-vaccine visits.

## **6.7. Study Variables and Their Measurement**

### **6.7.1. Study Primary Endpoints**

#### **Prevention of HIV Infection**

The acquisition of HIV infection. Detection of HIV-1 infection will be defined according to the HIV diagnostic algorithm (Section 6.7.3) utilizing serologic and nucleic acid technologies. Incidence of HIV infection will be compared in the vaccine and placebo-recipient groups.

And

#### **Changes in HIV-1 Viral Load**

Plasma viral load post-seroconversion is an important predictor of clinical progression of HIV infection and of transmissibility (54-56). The trial will quantitate HIV plasma viral load at the time of diagnosis and through the remainder of the follow-up period. Results will be compared in vaccine and placebo recipients who become HIV-infected during the trial. The trial is powered to detect a 0.39 log10 difference in viral load between vaccine and placebo recipients (see Section 6.9.3.2).

### **Secondary Endpoints**

#### **Changes in CD4 Cell Count**

CD4 counts add prognostic value to viral load in terms of rate of disease progression (57). Two CD4 cell counts will be obtained (at the verification blood draw and the notification blood draw) and through the remainder of the follow-up period. Results will be compared in vaccine and placebo recipients who become HIV-infected during the trial. The trial is powered to detect a 26% difference in CD4 count between vaccine and placebo groups (see Section

---

 Please see Analytic Addendum, **Section 18**, for primary analyses.

6.9.42).

### **Safety**

Reactogenicity, the frequency of local and systemic reactions, and both AEs and SAEs will be compared between vaccine and placebo groups (see Section 6.9.4.1).

### **Risk Behavior and Social Impacts**

Volunteers may believe that the vaccine is protective against HIV infection and therefore modify their behavior in such a way that they increase their risk of exposure to HIV. There are safeguards against such increases in HIV risk behavior. The first is the repeated counseling in regard to the vaccines' unproven efficacy, the use of placebos, behavioral risk reduction, along with HIV pre- and post-test counseling. Any risk-taking behavior reported during counseling will be noted and addressed, for example nonuse of condoms or use of IV drugs. The second is the use of baseline and interval behavioral risk assessments (which will be recorded on CRFs and entered into the database). Using these data, significant increases from baseline in risk-taking behavior noted among volunteers will be reported and interventions specifically designed to decrease this behavior will be implemented (see Section 6.9.4.1). In addition to being asked whether their risk behavior has changed over time, participants will also be asked whether they have experienced any favorable or unfavorable events associated with their participation in the vaccine trial. These participation impact events (PIEs) include employment, school or personal relationship problems or benefits, discrimination, and positive or negative health care experiences. If a participant does experience a PIE, its date and resolution status will also be recorded on the PIE CRF and entered into the database. Periodic assessment and review of both risk behavior change and PIEs will be carried out by the DSMB.

## **6.7.2. Safety Assessments**

### **6.7.2.1 Post-vaccination Events Monitored as Possible Reactions to Vaccine**

Selected local and systemic adverse events are routinely monitored in vaccine clinical trials as indicators of vaccine reactogenicity. These include (at the injection site) erythema, induration, pain/tenderness, swelling and limitation of arm movement, and (systemically) temperature, tiredness, myalgia, arthralgia, headache and rash and are herein termed "*post vaccination reaction*". It is recognized that each of these events, and particularly those of a systemic nature, may under some circumstances, in any individual subject, have another clearly defined diagnosis as a cause for these symptoms (for example, dengue fever). Those that have a clearly recognized cause not-related to the vaccination will not be reported as "*post-vaccination reactions*".

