### **Previous Studies with ALVAC-HIV Constructs and Subunit HIV-1 Env Vaccines**

Aventis Pasteur has utilized ALVAC vectors to express genes from rabies, measles, cytomegalovirus, Japanese encephalitis viruses and HIV. Clinical trials with these constructs have demonstrated safety and immunogenicity. In over 1800 subjects receiving ALVAC-HIV constructs, more local reactions have been observed in recipients of vaccine than placebo or control recipients; however, there were no differences observed in the occurrence of systemic reactions among these groups. Additionally, there was no difference in the rates of local and systemic reactions across the various ALVAC-HIV constructs evaluated.

Safety data were pooled from seven AIDS Vaccine Evaluation Group (AVEG) studies using ALVAC-HIV vCP205 (AVEG022, AVEG022A, AVEG029, AVEG032, AVEG034, AVEG034A, AVEG202) and one WRAIR study (RV124) (Aventis Pasteur unpublished data; End of Phase II safety package – Section 8). There were 809 subjects enrolled in the seven AVEG studies and 101 subjects enrolled in Study RV124, for a total of 910 subjects. In total, four deaths were reported, none of which were considered related to vaccination. In the AVEG studies, 170 of 809 subjects reported 233 SAEs to the NIAID Division of AIDS Regulatory Operation Center, 61 of which were considered potentially related to vaccinations. Of these 61 SAEs, 8 were definitely related, 10 were probably related and 43 were possibly related to administration of the different products. Upon further evaluation, of the 61 SAEs, 45 occurred in subjects in the vaccine treatment group, 2 in the control group and 14 in the placebo group. Of the 45 SAEs in the vaccine treatment group, 7 were definitely related, 10 probably related and 28 possibly related to vaccination. The 7 definitely vaccine-related SAEs included 4 episodes of

injection site reaction, 2 episodes of vasovagal reaction and 1 episode of a “cell-mediated allergic reaction”. None of these 7 definitely vaccine-related SAEs resulted in death or a life-threatening condition. In study RV124, there were 9 subjects reporting 9 SAEs; none were considered related to vaccination. Generally, ALVAC-HIV-associated reactogenicity events have been mild and transient in nature. Aside from local reactogenicity events, there have been no observed patterns of excess adverse events attributable to AVAC-HIV vaccination.

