### 6.7.2.2 Other Adverse Events

An adverse event (AE) is any undesired, noxious or pathological change in a patient or subject as indicated by physical signs, symptoms, and/or laboratory changes that occurs following administration of one of the vaccines, whether or not considered vaccine related. This definition includes intercurrent illnesses or injuries, and unexpected exacerbations of pre-existing conditions. Anticipated day-to-day fluctuations of pre-existing conditions that do not represent a clinically significant exacerbation need not be considered adverse events. Discrete episodes of chronic conditions occurring during a study period should be reported as adverse events in order to assess changes in frequency or severity.

History of all adverse events occurring up to visit 10 that have resulted in an encounter with a health care provider (physician, nurse, etc) will be elicited, recorded on source documents and transcribed onto CRFs. Adverse Events that are trauma-related can include less information, including less medication information, than do medical conditions. After visit 10, only AE's that are "medically significant" events, defined as requiring multiple visits (two or more) to a physician for the same condition, or that result in hospitalization or an emergency room visit, will be captured on source documents/CRF's. Medications will continue to be reported in association with AEs. Data on serious adverse events occurring through the whole period of the study will be collected and recorded on CRFs, as well as reported separately, per SOP, on SAE report forms. A subject with an SAE will be followed carefully until the condition is resolved or stabilized and/or chronicity is established. Any medication or other therapeutic measure taken to relieve symptoms of the medical problem will be recorded on the CRF with the report of the outcome on the SAE forms.

The *intensity* reported on the adverse event form will be determined by the research staff using the following guidelines:

- Mild (Grade 1):                      Transient or mild discomfort; no limitation in normal daily activity.
- Moderate (Grade 2):                Some limitation in normal daily activity.
- Severe (Grade 3):                    Unable to perform normal daily activity.
- Life threatening (Grade 4):        Life threatening
- Death (Grade 5):                    Death

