#### 6.9.4. Analysis of Secondary Endpoints

##### 6.9.4.1 Safety and Risk Behavior Data.

Reactogenicity, adverse events and serious adverse events will be tabulated both overall and by study arm. Frequencies of specific safety events will be compared across study arms using a chi-square test to evaluate the null hypothesis that safety event rates are the same in both study arms.

Risk assessment data from the ‘Baseline’ and ‘Interval’ Risk Assessment CRFs will be tabulated both overall and by study arm. These questionnaires collect reported behavior data. The data will be analyzed for changes in behavior. Frequencies of specific risk behavior events at baseline and during follow-up will be compared across study arms using chi-square tests to evaluate the null hypothesis that the event rates remain the same. Specific risk behavior events will be compared (see Behavioral Risk Assessment). Repeated measures analyses of binary data will be performed to evaluate changes in the prevalence of these behaviors over time, overall and between the treatment groups. In addition, changes over time in proportions exhibiting specific behaviors will be assessed using McNemar’s test. Participation impact events (from PIE CRFs) will also be tabulated overall and by study arm. Frequencies of events throughout the course of the study will be compared across study arms using chi-square tests to evaluate the null hypothesis that the event rates are similar in both study arms.

Previous studies using ALVAC-HIV (vCP1521) and AIDSVAX® B/E have shown that these vaccines alone and in combination (11,52) have good safety profiles. Previous and ongoing HIV vaccine studies conducted in Thailand have shown little evidence of increase in risk-taking behavior (27; TAVEG unpublished data). However, given the theoretical concern that antibodies generated by the prime-boost combination may prove to be enhancing, HIV infection rates in both groups will be monitored (as per previous analysis). In addition, the rate of disease progression as measured by viral load and CD4 count among infected vaccine recipients will be compared to the corresponding rates in placebo recipients.

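### Solicited reactions with another recognised cause are left out of the reactogenicity count: an unneeded causality filter in a placebo-controlled comparison, with a small capture gap and a possible but unproven bias

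*Protocol*

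**What the plan says.** Section 6.7.2.1 names the reactions that are solicited after each dose, local (such as erythema, induration and pain) and systemic (such as temperature, myalgia and headache). It notes that "each of these events, and particularly those of a systemic nature, may under some circumstances" have a different, well-defined diagnosis behind them, with dengue fever as the example. It then sets the rule: "Those that have a clearly recognized cause not-related to the vaccination will not be reported as" post-vaccination reactions.

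The safety paragraph under the secondary endpoints in Section 6.7.1 makes these counts a between-arm comparison: "Reactogenicity, the frequency of local and systemic reactions, and both AEs and SAEs will be compared between vaccine and placebo groups". Section 6.9.4.1 gives the test: "Frequencies of specific safety events will be compared across study arms using a chi-square test".

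Section 6.7.2.2 handles other adverse events differently. The definition applies "whether or not considered vaccine related". What is written down in the first year is limited, however: "History of all adverse events occurring up to visit 10 that have resulted in an encounter with a health care provider". Serious events are collected throughout.

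On earlier ALVAC-HIV studies, Section 4 says that "more local reactions have been observed in recipients of vaccine than placebo or control recipients", and that "there were no differences observed in the occurrence of systemic reactions among these groups".

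**The concern.** In a 1:1 randomised, placebo-controlled comparison, fevers and headaches from colds or dengue are expected equally often in both arms. Counting them all costs some background noise and needs no opinion about any single event. Removing some by presumed cause puts a judgement between the diary and the comparison, with three possible consequences:

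- The solicited event rate is understated.
- Some events have no stated place in either safety tabulation.
- If the judgement leans differently in the two arms, the comparison is no longer protected by randomisation. One possible cue is a local reaction recorded on the same diary, since local reactions were more frequent with vaccine in earlier studies.

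Reactogenicity is part of the secondary safety objective, so what is at stake is how cleanly the systemic reaction rates can be read. The efficacy conclusions are not affected.

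**Working it through.** **Where a solicited event ends up.** The protocol gives no figure to reproduce here, so the first check sets the capture rules side by side.

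| Solicited event in the 3-day diary | Reaction count (6.7.2.1) | Adverse event record (6.7.2.2) |
|---|---|---|
| No other recognised cause | Yes | Not needed for the reaction count |
| Other recognised cause, health-care encounter | No | Yes |
| Other recognised cause, no encounter, not serious | No | No stated route |
| Serious, any cause | Depends on cause | Yes, as a serious adverse event |

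The third row is the gap. The diary answer may still sit on a CRF, because Section 6.6 has diary findings entered at Visits 2, 4, 6 and 8. The protocol does not say that such an answer returns to any tabulation.

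For adverse events the protocol already takes the other approach. Section 6.7.2.2 has relatedness categories that include not related, and applies relatedness only in the analysis.

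**How much a lopsided filter could matter (illustration).** The arm size comes from Section 6.9.2: 16,000 allocated 1:1, so n = 8,000 per arm. The true systemic rate p and the excluded shares are not in the document and are assumed. There is no true difference.

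- Recorded rate in an arm = p × (1 − excluded share).
- SE = √[r₁(1 − r₁)/n + r₂(1 − r₂)/n], where r₁ and r₂ are the recorded rates.
- Chance of a significant two-sided 5% test ≈ Φ(|r₂ − r₁|/SE − 1.96).

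Example with p = 20%, excluding 10% of placebo and 2% of vaccine events:

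- Recorded rates are 0.20 × 0.90 = 18.0% and 0.20 × 0.98 = 19.6%.
- SE = √[(0.18 × 0.82 + 0.196 × 0.804)/8,000] = 0.0062.
- 0.016/0.0062 ≈ 2.59, and Φ(2.59 − 1.96) ≈ 74%.

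| True rate, both arms | Excluded, placebo / vaccine | Recorded, placebo / vaccine | Chance of significance |
|---|---|---|---|
| 10% | 5% / 2% | 9.5% / 9.8% | 9% |
| 20% | 5% / 2% | 19.0% / 19.6% | 16% |
| 20% | 10% / 5% | 18.0% / 19.0% | 37% |
| 20% | 10% / 2% | 18.0% / 19.6% | 74% |
| 40% | 10% / 2% | 36.0% / 39.2% | 99% |

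With equal exclusion, for example 10% in each arm at a true rate of 20%, both arms record 18.0%. That is an undercount of 2 percentage points and no false difference. The result therefore depends on how far attribution differs by arm, and the protocol is silent on that.

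**The case against.** The case for leaving the rule alone has real weight.

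- **The bar is high.** The section speaks of a well-defined other diagnosis and a clearly recognised cause, not a passing impression. Such a diagnosis will often involve a health-care encounter and so be recorded as an adverse event. This stands, and it makes the capture gap narrow.
- **The trial is blinded, and the cue is weak.** Site staff do not know the allocation. Diary review is scheduled one week after doses 1 to 3 (window −4 to +7 days) and two weeks after dose 4 (−2 to +14 days), so a visible arm reaction at that point is doubtful. The AIDSVAX placebo contains alum, which may narrow the local difference at doses 3 and 4. Who decides the cause, and when, is not stated. This stands. A diary entry remains a possible cue, but a weaker one.
- **Data are not necessarily discarded.** The rule governs what is reported as a reaction, and diary answers go onto a CRF. This stands. The loss is from the tabulations, not demonstrably from the database.
- **Tabulation choices belong in the SAP.** This holds only in part. The protocol fixes an exclusion rule here rather than leaving the matter open.

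A reader might infer more: that the filter would produce a significant systemic difference. One can build such a case with a 10% systemic rate in both arms, local reactions after 60% of vaccine and 30% of placebo doses, and retention of 90% of systemic events with a local reaction and 70% without:

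- Recorded rates are 0.10 × (0.6 × 0.9 + 0.4 × 0.7) = 8.2% and 0.10 × (0.3 × 0.9 + 0.7 × 0.7) = 7.6%.
- Over 32,000 doses per arm, z = 0.006/√(2 × 0.079 × 0.921/32,000) ≈ 2.8.

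The documents do not support that conclusion. Every rate is assumed. The nearest documented figure, 55% with pain or tenderness in the Thai AIDSVAX B/E trial, is per subject rather than per dose. Up to four doses come from one person, so they are not independent. At 8,000 per arm for a single dose the same inputs give z of only about 1.4.

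**Conclusion.** The point holds in a limited form. The exclusion is an avoidable causality judgement placed ahead of a randomised comparison. It understates solicited events and leaves minor, alternatively explained symptoms without an encounter outside both tabulations. Those two effects follow from the text alone.

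Bias between arms is a risk only. It requires attribution to differ by arm, which nothing in the protocol shows, and it is probably small given the blinding and the demand for a clear other cause. No magnitude can be derived from the document. The percentages above show sensitivity to assumed inputs and are not estimates for this trial. No sample size, alpha or power figure is affected. This is a cheap improvement, not an error that threatens a conclusion.

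**What to change.** Reword the end of Section 6.7.2.1 to say that all solicited local and systemic events recorded in the 3-day diary period are reported as post-vaccination reactions and compared by arm regardless of presumed cause. Record any presumed alternative cause in a separate field, and show the tabulation without alternatively explained events as supportive.

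Leave the encounter threshold for other adverse events in Section 6.7.2.2 as it is. It is a deliberate limit, and an adverse event form for every explained symptom would add far more work than this point justifies.

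The cost is a change of wording, one extra CRF field and slightly higher crude reaction rates in both arms. The diary already asks for the events. Sections 6.9.7 and 9.2 of this version refer to trial results, so vaccination-phase capture is already complete. For this trial the all-cause table would have to come from the existing diary CRFs, provided the excluded answers were kept there, which the protocol does not state.

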#### Instructions to Subjects Regarding Unusual or Severe Signs or Symptoms

Subjects will be given diary cards on which they are to answer questions about reactions that occur in the 3-day period after a vaccination. These will be returned to the district clinical site where they were vaccinated. All subjects will be instructed to seek medical attention by study personnel within the district where enrolled, if possible, or at another MOPH facility, if unusual or severe signs or symptoms occur after vaccination. Staff at health centers will refer volunteers to the district hospital for further evaluation and treatment as appropriate. These subjects, if possible, will be followed up clinically until resolution of symptoms.

### 6.7.2.2 Other Adverse Events

An adverse event (AE) is any undesired, noxious or pathological change in a patient or subject as indicated by physical signs, symptoms, and/or laboratory changes that occurs following administration of one of the vaccines, whether or not considered vaccine related. This definition includes intercurrent illnesses or injuries, and unexpected exacerbations of pre-existing conditions. Anticipated day-to-day fluctuations of pre-existing conditions that do not represent a clinically significant exacerbation need not be considered adverse events. Discrete episodes of chronic conditions occurring during a study period should be reported as adverse events in order to assess changes in frequency or severity.

History of all adverse events occurring up to visit 10 that have resulted in an encounter with a health care provider (physician, nurse, etc) will be elicited, recorded on source documents and transcribed onto CRFs. Adverse Events that are trauma-related can include less information, including less medication information, than do medical conditions. After visit 10, only AE's that are "medically significant" events, defined as requiring multiple visits (two or more) to a physician for the same condition, or that result in hospitalization or an emergency room visit, will be captured on source documents/CRF's. Medications will continue to be reported in association with AEs. Data on serious adverse events occurring through the whole period of the study will be collected and recorded on CRFs, as well as reported separately, per SOP, on SAE report forms. A subject with an SAE will be followed carefully until the condition is resolved or stabilized and/or chronicity is established. Any medication or other therapeutic measure taken to relieve symptoms of the medical problem will be recorded on the CRF with the report of the outcome on the SAE forms.

The *intensity* reported on the adverse event form will be determined by the research staff using the following guidelines:

- Mild (Grade 1):                      Transient or mild discomfort; no limitation in normal daily activity.
- Moderate (Grade 2):                Some limitation in normal daily activity.
- Severe (Grade 3):                    Unable to perform normal daily activity.
- Life threatening (Grade 4):        Life threatening
- Death (Grade 5):                    Death

The *relationship of vaccination* to adverse event (AE) will be determined based on the following definitions:

Not Related:

Vaccination administration and AE occurrence not reasonably related in time; OR  
AE obviously explained by another cause.

Unlikely Related:

Vaccine administration and AE occurrence remotely related in time; AND  
AE more likely explained by other causes than by vaccination.

Possibly Related:

Vaccine administration and AE occurrence reasonably related in time; AND  
AE explained equally well by causes other than vaccination.

Probably Related:

Vaccine administration and AE occurrence reasonably related in time; AND  
AE more likely explained by vaccination than by other mechanisms.

Definitely Related:

Vaccine administration and AE occurrence reasonably related in time; AND

Vaccination most likely explains the AE; AND  
AE is consistent with pattern of vaccine-related events.

(In analyses, vaccine-related AEs are defined as those AEs that are Possibly, Probably or Definitely Related to vaccination.)

A serious adverse event (SAE) is defined as any untoward medical occurrence that:

1. Results in death.
2. Is life threatening (i.e., the subject was, in the opinion of the investigator, at immediate risk of death from the event).
3. Requires or prolongs inpatient hospitalization. Hospitalization for either elective surgery related to a pre-existing condition that did not increase in severity or frequency following initiation of the study or for routine clinical procedures will not be considered an SAE.
4. Results in persistent or significant disability/incapacity (i.e., the event causes a substantial disruption of a person's ability to conduct normal life functions).
5. All pregnancies associated with congenital anomalies/birth defects.
6. Is an important and significant medical event that, based upon appropriate medical judgment, may endanger the subject and may require medical or surgical intervention to prevent one of the other outcomes defined above.

